### Exclusion criteria

The exclusion criteria for this study are as follows:Known or suspected food intolerances, allergies or hypersensitivity.Any bleeding disorder or taking medication which impacts blood coagulation.Known tendency towards keloid scarring.Known sensitivity or allergy to any local anesthetic medicines.Any reported use of substances which may pose undue personal risk to participants or introduce bias into the experiment.Any other condition or behavior deemed either to pose undue personal risk to participants or introduce bias into the experiment.

The sex of participants will be included in a stratified randomization scheme using a computer-based random number generator produced by an academic supervisor ([name]), who is not responsible for trial enrollment, nutritional preparation or provision. The only interaction by [name] with participants will be for obtaining muscle biopsies at baseline and follow-up, and thus he will be unaware of the assigned coding numbers to participants, rendering him unable to determine trial allocation to any participant. Details of the overall randomization scheme will only to be published once follow-up measurements are completed in order to complicate deciphering of the allocation sequence by those involved in trial enrollment [44].

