### Inclusion criteria

The inclusion criteria for this study are as follows:Both male and female volunteers.Aged between 18 and 48 years.Individuals free from cardiovascular, metabolic or joint disease as determined by a standard health questionnaire.No engagement in structured physical activity for more than two hours per week during the last two years.Nonsmoker.

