### Sample size estimation

*A priori* sample size estimation (G*power version 3.1.7, University Düsseldorf, Düsseldorf, Germany) from data in the literature similar to the proposed work [11], revealed that a total of 24 participants are required to achieve 90% power to detect a worthwhile increase in an endurance performance () of 5.3 ml · kg^−1^ and standard deviation of 3.3 ml · kg^−1^, using a two-tailed t-test for independent means with an alpha level of 0.05. Rolling recruitment of 32 participants in each phase of testing will therefore be conducted when considering an anticipated 15% dropout rate [11, 36].

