### Data analysis

The majority of data include measurements of cardiovascular and intramuscular markers of endurance training adaptations at baseline and follow-up, and thus treatments × time interactions will be explored using a general linear model with baseline included as a covariate, to account for any baseline imbalances because of regression to the mean [62]. The majority of variables in this experiment therefore involve a single comparison between two level scores, and so will not be adjusted for multiple comparisons across the different variables. Any data that require a single comparison of two means will be tested for normality using the Shapiro-Wilk test before using an independent t-test or non-parametric equivalent to examine differences between treatment arms (for example, magnitude of change in absolute and relative  between treatments). Relationships between outcome variables will be examined using a Pearson’s product-moment correlation and any meaningful associations (r ≥0.7) between baseline, and the magnitude of response to exercise training will be further explored by post-stratification of the treatment group according to baseline status. Significance will be set at ≤0.05 and all results being reported as the mean and standard error of the mean (SEM) unless stated otherwise.

Participants will be advised at the initial trial enrollment meeting to carefully consider the required investment of time and effort involved in the current project. This will be undertaken to minimize any negative impact associated with loss to follow-up, and consequently likely withdrawal can be made prior to randomization [63]. However, any unforeseen circumstances or withdrawal resulting in loss to follow-up will be documented and reported in the final trial report. In accordance, the handling of missing data subsequent to withdrawal will be primarily approached in a complete-case analysis adjustment method, while an imputation method will be considered where appropriate [64, 65].

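### Randomisation is stratified by sex but neither stated between-arm analysis includes sex; if sex predicts outcome beyond baseline, the tests are conservative and some power is lost

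*Protocol article*

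**What the plan says.** The randomisation paragraph, at the end of the Exclusion criteria section, states: "The sex of participants will be included in a stratified randomization scheme using a computer-based random number generator". No other stratification factor is named. The trial enrols both sexes (Inclusion criteria: "Both male and female volunteers"), but the expected mix is not given.

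The Data analysis section describes two between-arm analyses:

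- Treatment-by-time effects "will be explored using a general linear model with baseline included as a covariate". Baseline is the only covariate named.
- Where two means are compared, as for change in oxygen uptake, a normality test is followed by a comparison "using an independent t-test or non-parametric equivalent to examine differences between treatment arms". This adjusts for nothing.

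The one stratified analysis in that section is a possible split by baseline status, not by sex. The Sample size estimation section also rests on an unadjusted comparison, "using a two-tailed t-test for independent means with an alpha level of 0.05".

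**The concern.** Stratifying by sex balances the arms on sex, so the difference between men and women largely drops out of the treatment contrast. A model without sex leaves that difference in the residual and counts it as error. If it is real, the printed standard error exceeds the true one, confidence intervals are too wide, and the test rejects less often than its nominal 5%. The precision that stratification buys is then not used.

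Phases are small: 32 recruited in each, and about 27 expected to finish. The article names several primary outcomes (Approach to research questions: oxygen uptake, plasma albumin content, plasma volume, muscle genes and proteins) but states power for only one. Its own design treats sex as relevant, both by stratifying on it and by fixing the menstrual phase in which women are tested.

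**Working it through.** **1. The plan's own figure.** Inputs from Sample size estimation: difference 5.3, SD 3.3, two-sided alpha 0.05, 90% power, stated total 24. Equal allocation is assumed. The standardised difference is 5.3/3.3 = 1.606. Exact t-test power is 89.2% with 9 per arm, 92.4% with 10 and 96.4% with 12. The inputs therefore need 20 in total, not 24; 24 would give 90% if the SD were about 3.83. This is a separate matter and errs on the safe side. Dropout: 24/0.85 = 28.2, so 29 are needed and 32 covers it; 32 × 0.85 = 27.2 completers.

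**2. What omission does.** Let R be the share of residual variance (after baseline) explained by sex, with n per arm and sex balanced. The true SE is σ√(1−R)·√(2/n). The model without sex reports about σ√(2/n). The ratio is 1/√(1−R): 1.008 at R = 1.5%, 1.03 at 6%, 1.12 at 20%, 1.20 at 30%. With equal numbers of men and women, a gap of g within-sex SDs gives R = (g²/4)/(1 + g²/4): 1.5% for g = 0.25, 5.9% for 0.5, 20% for 1.

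**3. How much baseline already absorbs.** Assume the same sex gap at baseline and follow-up, within-sex variance 1 and within-sex correlation ρ. If sex explains a share S of total variance, put v = S/(1−S). The residual variance with baseline only is (1+v) − (ρ+v)²/(1+v); with sex added it is 1−ρ².

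- S = 30%, ρ = 0.8: v = 0.4286; 0.372 against 0.360. Residual share 3.2%, SE excess 1.6%.
- S = 10% or 20%, ρ = 0.8: residual share 1.1% or 2.2%, SE excess 0.5% or 1.1%.
- S = 30%, ρ = 0.6: 0.688 against 0.640. Residual share 7.0%, SE excess 3.7%.

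**4. Simulation with baseline in the model.** Sex-stratified allocation, equal sexes, 12 per arm, 4,000 trials per setting. The effect is 1 within-sex SD, and the gap is the sex difference left after baseline.

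| Gap (SD) | Mean SE without / with sex | Test size without / with sex | Power without / with sex |
|---|---|---|---|
| 0 | 0.413 / 0.413 | 5.0% / 5.0% | 62.9% / 62.8% |
| 0.25 | 0.417 / 0.413 | 4.8% / 5.0% | 62.1% / 62.1% |
| 0.5 | 0.426 / 0.412 | 4.2% / 4.7% | 61.2% / 63.1% |
| 1 | 0.466 / 0.413 | 3.1% / 5.3% | 53.0% / 61.9% |
| 2 | 0.601 / 0.414 | 0.7% / 4.9% | 29.2% / 61.9% |

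**5. The plan's own sample size inputs.** With 24 completers, SD 3.3 and one degree of freedom spent on baseline, power without sex is 96.3%. With sex added and the residual SD reduced to 3.3√(1−R):

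| R | 0% | 1.5% | 6% | 20% | 30% |
|---|---|---|---|---|---|
| SD 3.3 | 96.2% | 96.5% | 97.1% | 98.7% | 99.4% |
| SD 3.83 (without sex 89.9%) | 89.7% | 90.2% | 91.4% | 95.0% | 97.1% |

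These gains are slightly generous. Where power is high, balance on sex already helps the unadjusted estimate. Simulating SD 3.3 at R = 30% directly (4,000 trials) gave 97.1% without sex and 99.0% with it.

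**6. Where baseline cannot help.** According to Blood sampling, plasma volume is obtained as a change, from haemoglobin and haematocrit, so it has no baseline level to adjust for. The t-test on change uses no covariate. With 13 per arm (7/6 by sex), no baseline term, an effect of 1 total SD and sex explaining 10/20/30% of the analysed variance (8,000 trials per setting), test size without sex is 3.5/3.0/1.8%. Power is 69/71/70% without sex and 73/79/83% with it. With 32 randomised and 27 completing at random, size without sex is 4.2/3.2/2.4% and power is 70/72/72% against 73/79/84%, so the pattern survives dropout.

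**The case against.** The strongest reply is that the main model already adjusts for baseline, and for oxygen uptake or enzyme activity most of the difference between men and women is present at baseline. This stands, and it removes most of the effect for such outcomes (step 3). A reader might take a 30% sex share of total variance straight into the residual and infer a test size near 2% and a power loss of about 12 points for the main analysis. The article does not support that: those figures describe an analysis without the baseline term.

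Second, the powered endpoint has room to spare on its stated inputs, and the sample size never relied on adjusting for sex. This also stands for that endpoint. It does not cover the other primary outcomes, for which no power is given.

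Third, this is a condensed article, the text does not say that baseline is the sole covariate, and an analysis plan could add sex. It could. But the article goes as far as naming its model and covariate, and the design factor is not there. The point is an improvement to a stated model, not a complaint about missing detail.

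**Conclusion.** The mismatch is in the text: sex is used to randomise and is absent from both stated analyses. The consequence is conditional. If sex predicts the outcome beyond baseline, standard errors are too large and tests conservative; if it does not, nothing is lost. A reader might infer that power is certainly being lost, or that the error rate or the estimate is compromised. Neither follows. No sex effect is documented, type I error falls rather than rises, and under the stratified allocation the omission does not bias the treatment effect.

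For level outcomes the likely loss is small: SE excess about 0 to 4% and power loss about 0 to 2 points, for a residual sex gap up to about half an SD. On the stated sample size inputs the gain from adding sex is at most about 3 points at a 30% residual share; it would be about 7 if the SD were 3.83. The loss reaches roughly 8 to 13 points, for a 1 SD effect, only if sex explains 20 to 30% of residual or change-score variance. That is least protected against in plasma-volume change and the t-test on change. All sizes assume equal arms, near-equal numbers of men and women, and sex effects that the article does not give.

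**What to change.** State in the Data analysis section that sex, as the stratification factor, is a fixed effect in every between-arm model:

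- outcomes with a baseline level: follow-up = arm + baseline + sex;
- plasma-volume change: change = arm + sex.

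Use these models in place of the unadjusted t-test on change. If a rank-based fallback is kept, stratify it by sex as well. Fix the wording before follow-up data are analysed, so that the covariates are not chosen on the results.

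The cost is one degree of freedom. At 24 completers the critical t moves from 2.080 to 2.086, about 0.3%, and power is essentially unchanged if sex explains nothing (96.3% to 96.2% on the stated inputs). The adjustment also corrects any imbalance by sex that dropout leaves.

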### Experimental design

The proposed project involves two distinct phases of testing, each contrasting two nutritional interventions in a randomized investigator-participant double-blind parallel group design. The independent variable will be the precise nutritional intervention ingested following exercise in Phase I, while timing of ingestion will be the independent variable in Phase II. Specifically, those participants recruited for Phase I (n =32, approximately) of testing will receive a supplement containing carbohydrate (sucrose) plus protein (whey protein hydrolysate) at an ingestion rate of 0.4 and 0.4 g · kg BM^−1^ respectively. The second group will be a control group, whereby an ingestion of an isocaloric carbohydrate supplements will be assigned (0.8 g · kg BM^−1^). The two nutritional interventions provided in Phase II (n =32, approximately) will be identical (0.4 g · kg BM^−1^ carbohydrate +0.4 g · kg BM^−1^ whey protein hydrolysate), while the timing of intake will be manipulated. A group will ingest the carbohydrate-protein supplement immediately post-exercise and one hour later, while the overnight recovery group will receive the supplements one hour prior to sleep, and at 02:00, as an overnight nutritional intervention. The nutritional information for the supplements is provided in Table 1.

**Table 1 Tab1:** **Nutritional information of the supplements provided in Phase I and Phase II of the trial**

	High sucrose	Sucrose + whey protein hydrolysate
**Sucrose (g/l)**	80	40
**Lactose (g/l)**	-	≤2.3*
**Protein (g/l)**	-	40
**Fat (g/l)**	-	≤2.4*
**Sodium (g/l)**	-	0.72
**Potassium (g/l)**	-	0.10
**Calcium (g/l)**	-	0.15
**Magnesium (g/l)**	-	0.01
**Phosphorous (g/l)**	-	0.19
**Chloride (g/l)**	-	0.29
**Energy (kcal/)**	320	320

*Assay unable to detect values below this number. The caloric content for fat and lactose was therefore assumed to be negligible.

Supplements will be provided in a sachet form along with shaker bottles with measurement scales. Solution preparation will be instructed to participants to achieve a volume of ingestion of 10 ml · kg BM^−1^. The entire protocol will be eight weeks duration and will consist of: (i) a baseline testing week with two exercise sessions, (ii) the first, second and third weeks of training at 70% , (iii) the fourth, fifth and sixth weeks of training at 75%  and (iv) a final week for follow-up measurements. A total of 26 endurance-based training sessions will be prescribed for each participant.

### Baseline testing

Prior to the start of the training period, participants are required to attend the laboratory on two occasions. The first visit will include anthropometric assessment of height, weight and body mass. Participants will also undergo an assessment of their running economy ( · km^−1^) and  (details provided below). The second preliminary visit will then be arranged within a week following the first laboratory visit. A 48-hour standardization of lifestyle will be employed (discussed below). This visit will involve obtaining fat mass percentage using bioelectrical impedance analysis (BIA), followed by a resting expired gas sample to measure resting metabolic rate (RMR). After laying on a semi-supine bed for five minutes, two five-minute baseline resting expired gas samples will be taken for the estimation of RMR, along with resting heart rate via short-range telemetry (Polar FT2, Kempele, Finland). A venous blood sample (10 ml) will also be obtained from an antecubital vein to measure different plasma metabolites, in addition to hematological parameters for the estimation of plasma volume change. Subsequently, an 80 to 100 mg muscle biopsy sample will be obtained from the vastus lateralis under a local anesthetic (1% lidocaine; Hameln Pharmaceuticals Ltd., Brockworth, United Kingdom). In relation to eumenorrheic female participants, all measurements will be conducted three to 10 days after the onset of menses (follicular phase) to ensure low levels of circulating female hormones and therefore minimize any measurement errors associated with menstrual cycle [45]. Two exercise sessions will then be employed during the baseline testing week that require participants to run on a motorized treadmill for 30 minutes per day. These were aimed to allow participants to gauge the relative intensity required during their prescribed training intervention, while also familiarizing them with treadmill running, before the commencement of the six weeks training intervention.

### Training intervention

Exercise sessions performed in the baseline testing week will last for 30 minutes and thereafter the duration of sessions will progressively increase to 40, 50 and 60 minutes in week one, weeks two to three, and weeks four to six, respectively. Prior to any exercise session, a five-minute warm-up at 60%  will be superimposed, followed by treadmill running at a speed corresponding to 70%  for the durations indicated above. The target %  will be attained by providing participants with their relative speeds at any given intensity during the training intervention, which will be determined by linear regression (Excel 2010, Microsoft, Redmond, Washington, United States) during the first baseline visit. During the midpoint (training week three), the speed will be increased to elicit 75% . Only water consumption will be permitted during exercise sessions, which will be consumed *ad libitum*. Upon cessation of each exercise session in Phase I, a post-exercise nutritional supplement will be ingested immediately, while a second bolus will then be consumed one hour after the end of exercise. In relation to Phase II of testing, one group will ingest a post-exercise nutritional supplement in a similar manner to Phase I, while the other group will ingest an identical supplement one hour prior to sleep and at 02:00. During the nutritional provision periods, participants will be instructed to consume only water to avoid any confounding results relating the outcome variables of the study. Once every fortnight, participants will report to the laboratory to provide the nutritional supplements for the subsequent two-week training block, with a total of three scheduled meetings throughout the training intervention. This visit is also to confirm the adherence of participants to the prescribed training and supplementation procedures.

Although several risk factors will be screened before participants take part in exercise, the prescribed physical exercise may increase the risk of certain adverse events (such as myocardial infarction, musculoskeletal injuries and so on). Nevertheless, the prescribed endurance training will be conducted in a gymnasium under supervision of trainers who are familiar with first aid procedures, and the occurrence of any adverse events related to the study will be reported.

### Follow-up testing

The follow-up procedures after the training intervention will be identical to those in the baseline testing phase of the experiment (Figure 1). Importantly, the interval between the final session of prescribed training and follow-up measurements will be kept as close as possible to avoid any de-training effects [35]. Namely, measurements of running economy and  will be taken at least one, and at most two days, following the final exercise training session. This will be followed by 48 hours of standardization of lifestyle (replicating procedures of dietary records and activity obtained two days before baseline measurements) before obtaining any measurement pertaining to the second follow-up laboratory visit, a period of sufficient length to separate the chronic effects of training from exercise-induced responses [46].

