## Methods/Design

### Approach to research questions

The primary outcomes of this trial are the assessment of cardiovascular (changes in , plasma albumin content and plasma volume) and intramuscular (selected genes and proteins involved in cellular adaptive processes) training-induced adaptations, and whether protein co-ingestion (immediate or overnight) improves the magnitude of these adaptations. In accordance, two phases of testing will be conducted.

Phase I will be addressed by evaluating a carbohydrate-protein mixture against an energy-matched carbohydrate control to examine the influence of post-exercise protein intake in enhancing endurance training adaptations. Participants in Phase I will be randomly allocated to a group receiving an isocaloric carbohydrate supplement or a group receiving a carbohydrate-protein supplement, in a randomized investigator-participant double-blind manner, whereby the chief investigator ([name]) and participants will be blinded from the trial allocation. The acute post-exercise phase is important when considering the metabolic priority for recovery to be initiated [3, 21] and the potentiated sensitivity to nutritional interventions during this period [22]. It has been established that glycogen resynthesis and amino acid uptake rates are augmented following an exercise bout, and that the ingestion of carbohydrate and protein stimulate this process [6, 23–25]. This has subsequently prompted large numbers of studies to investigate the role of combined carbohydrate-protein ingestion in restoring glycogen stores, potential attenuation of decrements of skeletal muscle functional integrity and subsequent exercise performance [12, 26]. It is now generally accepted that incorporating protein into a post-exercise feeding regimen is a viable strategy to enhance recovery, mainly through observations in acute based studies [7, 8, 21, 27–33]. Yet, the effects of protein ingestion are more likely to be realized beyond the acute recovery phase, given that upregulation of endurance exercise-specific gene expression peaks between 10 and 24 hours following an exercise bout, and may surpass 96 hours for muscular recovery and adaptive remodeling to occur, suggesting that repeated bouts of exercise are required to detect worthwhile training adaptations [3, 34].

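### The gap between the maximal run and the blood and biopsy visit is a nominal 48 h at follow-up but any time within a week at baseline, so the pre-to-post change in several primary outcomes rests on unmatched timing

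*Protocol article*

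**What the plan says.** The Baseline testing section places the running economy and maximal oxygen uptake tests at the first laboratory visit, and the resting, blood and biopsy measurements at the second. On the gap between them it says: "The second preliminary visit will then be arranged within a week following the first laboratory visit". It gives no minimum, but asks for 48 hours of lifestyle control before the second visit.

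The Follow-up testing section opens with: "The follow-up procedures after the training intervention will be identical to those in the baseline testing phase of the experiment". It then gives its own timing. The running tests "will be taken at least one, and at most two days, following the final exercise training session". For the second visit: "This will be followed by 48 hours of standardization of lifestyle". That period is described as "a period of sufficient length to separate the chronic effects of training from exercise-induced responses", with a citation. The section also asks that follow-up testing stay close to the last session, to limit detraining.

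The Approach to research questions section lists plasma volume, plasma albumin content and the muscle gene and protein panel among the primary outcomes. The same section says that endurance-specific "gene expression peaks between 10 and 24 hours following an exercise bout" and that the process "may surpass 96 hours for muscular recovery and adaptive remodeling to occur".

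**The concern.** These outcomes are presented as adaptations to six weeks of training, read from one sample before and one after. Each sample follows a run to exhaustion. If the time since that run is about two days at follow-up but anything up to a week at baseline, the change can contain a fading response to the run as well as the training effect. Because the baseline gap also varies between participants, it adds spread that has nothing to do with training.

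Timing enters some outcomes directly. Under Blood sampling, the change in plasma volume is computed from hemoglobin and hematocrit at the two time points, and albumin content is derived from that change. Under Data analysis, the baseline value is the covariate in the main model, changes are also compared directly, and participants may be post-stratified by baseline status. With about 32 participants per phase, avoidable noise in the baseline value is worth removing.

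**Working it through.** **Inputs**
- Baseline, maximal run to blood and biopsy: at most 7 days, no minimum (Baseline testing).
- Follow-up, last training session to maximal run: 1 to 2 days; maximal run to blood and biopsy: 48 h, no upper limit stated (Follow-up testing).
- One baseline week (Experimental design), with two treadmill sessions that follow the second visit (Baseline testing).
- Gene-expression peak at 10 to 24 h; recovery and remodeling possibly beyond 96 h (Approach to research questions).

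The plan's only figure here is the 48 h, which is stated and not derived, so there is no formula to reproduce.

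**Intervals**
1. Follow-up, run to sampling: 48 h (nominal).
2. Follow-up, last training session to sampling: 24 + 48 = 72 h, to 48 + 48 = 96 h.
3. Baseline, run to sampling, ceiling: 7 × 24 = 168 h. Largest difference: 168 − 48 = 120 h.
4. Baseline if the first visit opens the baseline week and the two sessions take days 6 and 7 (an assumption; the text does not say so): second visit by day 5, so (5 − 1) × 24 = 96 h. Difference: 96 − 48 = 48 h.
5. Baseline minimum: 48 h only if the lifestyle control starts after the first visit, which is not stated. The mismatch could therefore run in either direction.

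**Where the mismatch goes**

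Let r(t) be the residual response t hours after the run, t_b the baseline gap and t_f the follow-up gap.

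- Within a participant: observed change = training effect + r(t_f) − r(t_b). If t_b = t_f, the last two terms cancel to the extent that the response to such a run is the same before and after training. If t_b differs from t_f, they do not cancel even then.
- Between arms: no supplement has been taken at baseline and both arms use the same booking rule, so the average of r(t_b) is the same in both arms by randomization and drops out of the difference. What remains of r(t_b) is its spread, which weakens the correlation between baseline and follow-up and so the precision gained from the covariate.

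The documents give no values for r, so neither effect can be sized.

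**The two statements on duration**

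At 48 h the sample is past the 10 to 24 h peak. The run (48 h) lies inside 96 h, and the last session (72 to 96 h) lies inside it or at its edge. Passing a peak is not the same as returning to the resting level, so the Approach section does not support an unqualified statement that 48 h is enough. It does not refute it either.

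**The case against.** Four counter-arguments carry weight.

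**The lifestyle control is matched.** Both second visits follow 48 hours of controlled diet and activity, and the word identical may refer only to procedures; it points to a figure that is not shown here. This is fair as to wording. But the control governs the two days before sampling, not the time since the run, so the interval stays unfixed at baseline.

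**The 120 h is a ceiling.** This stands. The single baseline week may well shorten the gap, and the follow-up 48 h is itself nominal. A reader should not take 120 h as typical.

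**The treatment comparison is protected.** This also stands. A reader might infer that the unequal intervals bias the effect of protein or of its timing. The documents do not support that: both randomized arms share the schedule. A reader might further infer that an arm difference could reflect recovery from the last supplemented session. That question does not depend on the baseline interval, matching the visits would leave it untouched, and the article openly trades it against detraining.

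**The 96-hour figure is no washout rule.** A reader might infer that the article contradicts itself, or that the follow-up sample always falls in an acute window. That goes too far. The figure is hedged, concerns recovery and remodeling, is used to argue for repeated bouts, and shares its sentence with a peak that 48 h clears. The sufficiency statement also rests on a cited source that is not at hand. What remains is a tension in wording.

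**Conclusion.** The interval mismatch is real on the face of the text: a nominal 48 h at follow-up against any time within a week at baseline. The difference is up to 120 h by the wording, and about 48 h if the first visit opens the baseline week and the two sessions fill its last two days. It affects the pre-to-post reading of plasma volume, albumin content and the muscle markers, and it costs some precision through a noisier baseline value. It is not a direct source of bias between arms. Whether the loss is material depends on how much response to a maximal run persists from two days onward, which the documents do not say. The point is a worthwhile improvement in measurement timing and does not threaten the trial's main comparison. The statement on 48 h sufficiency is a secondary matter of wording.

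**What to change.** In Baseline testing, replace the within-a-week rule by the interval used at follow-up: the second visit about 48 h after the maximal run, with the same stated tolerance at both time points. Record the actual hours from run to sampling for every participant, including those in Phase I, which has already started recruiting. Phase II recruitment is still to come, so the rule can apply there from the first participant.

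In Follow-up testing, qualify the sentence on 48 h so that it is consistent with the remark on 96 hours in the Approach section, or explain why the two concern different processes.

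The change needs no extra visit, sample or staff. The cost is less freedom in booking. For eumenorrheic women, whose measurements must fall 3 to 10 days after the onset of menses, a two-day gap leaves the first visit days 3 to 8 (10 − 2 = 8). The medical clearance for local anesthetic must also be in hand in time for the biopsy. Matching the intervals equalizes the time since the maximal run; it does not remove any residual effect of the last training session.
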